## Abstract

**Background:**

Estimates show that as many as one in 10 patients are harmed while receiving hospital care. Previous strategies to improve safety have focused on developing incident reporting systems and changing systems of care and professional behaviour, with little involvement of patients. The need to engage with patients about the quality and safety of their care has never been more evident with recent high profile reviews of poor hospital care all emphasising the need to develop and support better systems for capturing and responding to the patient perspective on their care. Over the past 3 years, our research team have developed, tested and refined the PRASE (Patient Reporting and Action for a Safe Environment) intervention, which gains patient feedback about quality and safety on hospital wards.

**Methods/design:**

A multi-centre, cluster, wait list design, randomised controlled trial with an embedded qualitative process evaluation. The aim is to assess the efficacy of the PRASE intervention, in achieving patient safety improvements over a 12-month period.

The trial will take place across 32 hospital wards in three NHS Hospital Trusts in the North of England. The PRASE intervention comprises two tools: (1) a 44-item questionnaire which asks patients about safety concerns and issues; and (2) a proforma for patients to report (a) any specific patient safety incidents they have been involved in or witnessed and (b) any positive experiences. These two tools then provide data which are fed back to wards in a structured feedback report. Using this report, ward staff are asked to hold action planning meetings (APMs) in order to action plan, then implement their plans in line with the issues raised by patients in order to improve patient safety and the patient experience.

The trial will be subjected to a rigorous qualitative process evaluation which will enable interpretation of the trial results. Methods: fieldworker diaries, ethnographic observation of APMs, structured interviews with APM lead and collection of key data about intervention wards. Intervention fidelity will be assessed primarily by adherence to the intervention via scoring based on an adapted framework.

**Discussion:**

This study will be one of the largest patient safety trials ever conducted, involving 32 hospital wards. The results will further understanding about how patient feedback on the safety of care can be used to improve safety at a ward level. Incorporating the ‘patient voice’ is critical if patient feedback is to be situated as an integral part of patient safety improvements.

**Trial registration:**

ISRCTN07689702, 16 Aug 2013

**Electronic supplementary material:**

The online version of this article (doi:10.1186/1745-6215-15-420) contains supplementary material, which is available to authorized users.

## Background

The public expect safety to be a priority within health services. However, estimates show that as many as one in 10 patients are harmed while receiving hospital care
[1–4]. Healthcare associated harm is defined as arising from or associated with plans or actions taken during the provision of healthcare, rather than an underlying disease or injury
[5]. One study of admissions analysed over a 5-year period across 10 hospitals in the Unites States
[6] found that 63% of all harms were deemed preventable. The recent UK NHS Mandate
[7] lists one of its core themes as: ‘treating and caring for people in a safe environment and protecting them from avoidable harm’, with the objective of reducing avoidable harm and embedding a culture of patient safety in the NHS by 2015. Accordingly, patient safety has been firmly positioned as a key NHS and government concern. Patient involvement in healthcare safety is also a policy priority with, for example, the World Health Organization’s World Alliance for Patient Safety (WHO, WAPS) citing mobilisation and empowerment of patients as one of six action areas that will be taken forward in its ‘Patients for Patient Safety’ programme
[8].

Strategies to improve safety have focused on developing incident reporting systems, and changing systems of care and professional behaviour. However, there has recently been a growing interest in involving patients in safety initiatives. This reflects recent UK government policy aims for people to be generally more involved in their care
[9, 10]. High profile reviews of poor UK hospital care
[11–13] have all emphasised the need to develop and support better systems for capturing and responding to the patient perspective on their care. However, it is imperative that such systems are robustly developed and evaluated, and moreover, integrated into existing clinical governance systems within healthcare organisations
[14].

Despite international emphasis on patient involvement in safety there is a dearth of research evidence on the acceptability of this involvement to patients and equivocal evidence to date on whether such involvement leads to improvements in safety. The evidence that exists indicates that patients are willing and able to participate in error prevention strategies
[15] which have the potential to improve safety
[16–19]. However, many factors hinder patient participation including acceptance of the new patient role, lack of medical knowledge, lack of confidence, co-morbidity and sociodemographic factors
[20]. Thus, there is clearly a need to understand further how patients can best be involved in safety initiatives and the effectiveness of such involvement in improving safety.

Reason’s model of organisational safety
[21] states that organisational accidents are a result of a number of factors including active failures on the part of the individual (for example, attentional slips, or mistakes in decision making), and ‘systems failures’ encompassing latent failures (for example, budgeting or rostering decisions) and local working conditions (for example, equipment unavailable, ward or unit understaffed). Systems failures are often referred to as ‘contributory factors’. Based on these ideas, measurement tools have been developed in high-risk industries to monitor organisations’ ‘safety health’
[22, 23]. However, currently no general means of assessing organisational safety or ‘systems’ failures exists within the NHS. Furthermore, no specific measures of organisational safety exist that ask for the views of patients, despite patients being well placed to observe the organisation of their care and the practices around them. Therefore, there is a need for reliable and valid tools that allow patients the opportunity to provide feedback on the safety of their care environment to inform local and organisational changes to improve patient safety.

Learning from error is a key element of patient safety
[24], and one way to learn is through the reporting and analysis of patient safety incidents. A patient safety incident (PSI) has been defined as ‘any unintended or unexpected incident which could have or did lead to harm for one or more patients receiving NHS care’
[25]. This definition usefully encompasses a variety of situations relating to patient safety, across both adverse events themselves and near misses. Historically, efforts to learn from incident reports have been focused on staff-led reporting systems
[26], with little attention paid to the potential of the patient as a valuable source of information about patient safety
[18, 27–30]. Indeed, it has been argued by some authors that the patient is uniquely placed to contribute to the quality and safety of their own care
[31], with recent empirical work demonstrating the feasibility and value of patient reporting
[32–35]. However, no study to date has attempted to systematically develop and evaluate the most effective method of patient reporting. In addition, no study has attempted to link reporting of patient safety incidents to mainstream quality improvement mechanisms.

During the last 3 years, our research team have developed and tested the Patient Measure of Safety (PMOS)
[36, 37] and the Patient Safety Incident Reporting Tool (PIRT). Together, these tools form the PRASE (Patient Reporting and Action for a Safe Environment) intervention which asks patients about the safety and quality of their care. PMOS is a 44-item questionnaire and PIRT is a reporting proforma. Patient feedback is collated into a report from which ward staff formally action plan and implement changes - in line with the issues raised by patients - with a view to improving patient safety and the patient experience. More detail about the intervention is given in the Methods section.

PRASE has recently been piloted in a trial of over 300 participants in a medium-sized hospital in the North of England. This pilot has allowed the research team to test key feasibility, usability and logistical issues. Much of the development of the intervention to date and associated work has been published elsewhere
[36–38]. This paper provides the protocol for the current study which will test the PRASE intervention in a multi-centre, cluster randomised controlled trial, employing a wait list design.

## Methods/design (trial)

### Primary objective

To assess the effectiveness of the PRASE patient safety intervention, in achieving patient safety improvements over a 12-month period.

### Design

A multi-centre, cluster randomised controlled trial, randomising wards to either intervention or control in a 1:1 ratio.

### The PRASE intervention process

The PRASE intervention is designed to collect feedback from patients about the safety of their care, using robust tools developed within our team over the past 3 years. This patient feedback is then collated and presented to each ward in a formal report (a ‘feedback report’). This report then allows ward staff to understand more about how patients perceive the safety of their care on their ward, and then target improvements based on problematic areas. The philosophy of this intervention is that it is an iterative process with a cycle of measurement, feedback and change lasting for a period of 6 months. The three key stages of the process are: a) measurement, b) feedback, c) action planning and change.

a) Measurement

Over a 3- to 4-week period, an average of 25 patients per ward will be recruited to participate in the measurement phase. Each patient (deemed to have capacity to consent) will be approached, the study explained, and informed consent taken. Following this, and using a computer tablet, the research fellow or research nurse will ask the patient to complete the 44-item PMOS questionnaire, and report any safety concerns (or specific positive experiences of care) using the PIRT incident reporting tool. The 44-item questionnaire asks questions based on eight different domains which are:

communication and team workingorganisation and care planningaccess to resourcesward type and layoutinformation flowstaff roles and responsibilitiesequipmentdelays

An additional four questions are asked, which are described under the Secondary Outcomes section. Patients will be given a choice of whether they would prefer to self-complete the questionnaire or have it facilitated by the researcher. Patient reports of safety concerns (or positive reports) can only be recorded in a facilitated conversation with a researcher, due to the need to elicit detailed information in a specific format that needs to be typed onto the computer tablet. The PMOS questionnaire and PIRT tool are detailed in Additional file
1: Appendix 1 and Additional file
1: Appendix 2.

There are three measurement periods – at baseline, at 6 months, and a final measurement at 12 months.

b) Feedback

Following the measurement period, the information for each ward will be collated and presented to the ward in the form of a ‘Feedback Report’. This report provides a variety of different qualitative and quantitative information for staff, and has been designed and piloted by a team of patients, academics and health professionals to be as user friendly as possible. Please see Additional file
1: Appendix 3 for an example of the feedback report.

The report provides an overall ward safety profile (on pages 3 and 4) which summarises scores and number of reports (concerns or positive experiences) relating to each contributory factors domain of the PMOS questionnaire, as well as providing a breakdown of how these scores and reports relate to specific questions. PMOS questionnaire scores are shown graphically using a traffic light system to allow staff to see where they are performing well, and where improvements are necessary.

No recommendations for areas of action are suggested by the research team. The feedback report is simply a reflection of the patient’s perspective of the safety of their care. It is then up to ward staff to identify areas to target for improvement, within the next phase of the intervention.

c) Action planning and change

The next phase of the intervention is action planning, followed by implementing and monitoring changes, based on the areas identified for action in the feedback report. To undertake the action planning, we will ask participating wards to identify an Action Planning Team (APT). This team will comprise a minimum of four people who work on the ward, and ideally include both senior and more junior staff, from different professional groups. An example action planning team might include any of the following representatives: matron, consultant, ward manager/ward sister, junior doctor, staff nurse, healthcare assistant, Allied Health Professional (for example, a physiotherapist, an occupational therapist), pharmacist, ward clerk or patient representative. The APT will be responsible for receiving the feedback report, considering which area(s) should be targeted, and agreeing an action plan for improvement. In addition, the team will need to monitor the implementation of the plan. A nominated person within the APT will take responsibility for delivering the action plan.

Action Planning Meetings (APMs) will be facilitated by a senior researcher from the Quality & Safety research team. The piloting of the PRASE intervention showed that facilitation of APMs was important for generation of concrete action plans as an outcome of the action planning meeting.

Control wards will receive no intervention during the study duration. At the end of the study, control wards will receive all their feedback reports for the three time points of data collection amalgamated into one report.

### Setting and sample

This study will be undertaken within 32 hospital wards, spread across three NHS Trusts, over five different hospital sites (eight wards at a small district general hospital, 10 wards at a medium sized teaching hospital and 14 wards at a very large teaching hospital). Study participants will be patients within participating wards. An average of 25 patients within each ward will be recruited at three different time points across the study period. Each time point lasts 3 to 4 weeks and data collection occurs within the same 3- to 4-week window for all participating wards in the same Trust. The eligibility criteria for the study are given below but, briefly, the selection criteria for participation is: any patient aged 16 years or over who has capacity to give informed consent to take part. All patients who satisfy the eligibility criteria are approached and then if they agree to take part in the study and give informed consent then they are recruited into the study. Therefore, selection bias is minimal as researchers approach every patient on the ward in a stepwise fashion, unless the patient does not have mental capacity to give informed consent or they are so gravely ill or distressed to the extent that it would preclude the researcher undertaking the PMOS questionnaire with them. Recruitment of patients on a ward ceases when 25 patients have been recruited. The study will involve 800 patients at each time point and equates to a total sample of 2,400 patients. While study participants are patients, the outcome measures are at ward-level meaning that the unit of analysis is the ward.

Wards will be randomly assigned to either the intervention or control groups, on a 1:1 ratio. Randomisation will be carried out by York Trials Unit Randomisation Service (based at the University of York) using a secure computer system. All wards from each Trust will be randomised in a batch. Although there is the possibility of staff moving between control and intervention wards in a hospital, the possibility of contamination between the groups is expected to be minimal. This is because the ‘Feedback Report’ is not available to control wards and the intervention is ward-specific dependent on this. Baseline data collection will be undertaken at least 1 month before randomisation to ensure completion of data collection before knowledge of randomisation. Once baseline data have been collected in a Trust, participating wards will be randomly allocated to one of the two arms: intervention or control. Minimisation will be used to balance the groups with respect to ward specialty, average age, single/mixed sex wards and ward size. After randomisation, ‘start up’ meetings will be held with intervention wards only. Intervention wards will be asked to set up action planning meetings in order to consider their first feedback report. The above process is detailed in flow chart format in Additional file
1: Appendix 4.

### Blinding

Data collectors will be blind as to which wards are in the intervention group and which are in the control group, in order to minimise bias in data collection. Blinding of the senior researchers working on this study is not possible as they are facilitating the action planning meetings which take place with intervention wards only.

### Inclusion criteria

Male or femaleAged 16 years or overAble to give informed consentMinimum period of 4 h on the ward before questionnaire administered

### Exclusion criteria

Does not have capacity to consentChild under the age of 16 yearsHas capacity but is too ill or distressed to take part (for example, breathlessness, pain, bleeding, immediately postoperative)Has already taken part in the study within the previous month

### Estimate of sample size

The study will be powered to detect a small to medium difference (effect size = 0.3) between the intervention and control groups with respect to the Patient Safety Thermometer score (See Outcome Measures for explanation of this score). A small to medium effect size seems a reasonable assumption as each ward will be focussing on developing and implementing their own action plans, tailored using their initial feedback. The intervention is therefore specific to individual wards and may not impact on all areas measured by the Patient Safety Thermometer. In order to achieve 80% power (with alpha = 0.05) with an average cluster size of 25 patients and assumed ICC of 0.05, 32 wards will be required (16 per arm). This estimate of ICC seems reasonable for a trial in secondary care with a patient reported outcome
[39].

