### Trial analysis

A full Statistical Analysis Plan will be written prior to any analyses. Analyses of individual level outcomes will account for clustering. For the primary outcomes, the difference between intervention groups will be estimated with 95% confidence intervals. The intervention groups will be compared with respect to the proportion of harm-free care across wards at 12 months. A linear regression model accounting for the minimisation factors and the baseline level of harm-free care will also be included as a covariate. As the outcome measure is on a ward level, no adjustment for clustering is required. The difference between the intervention groups at 12 months will be calculated with a 95% confidence interval. The standardised effect size will also be reported.

Multi-item PMOS domains will be treated as continuous data in the analysis. Linear mixed models accounting for the minimisation factors and baseline PMOS scores (ward level averages) will be used to compare the intervention groups with respect to each domain score at 12 months. Random effects will be used to account for the clustering at ward level. The difference in adjusted (least square) means will be summarised with 95% confidence intervals. Standardised effect size and ICC will also be calculated. Due to the nature of the intervention it is not possible to identify which domains are of primary interest, since the intervention across different wards may focus on improving different domains. Each domain will therefore be tested without adjustment for multiplicity. Interpretation of the *P* values will be considered carefully alongside the full details of which domain(s) the interventions in each ward were aiming to improve.

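### The only power statement is attached to the Safety Thermometer score, but its inputs describe the patient-level PMOS questionnaire; the power for harm-free care is therefore not established

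*Protocol article*

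**What the plan says.** In the protocol article, 'Estimate of sample size' states: "The study will be powered to detect a small to medium difference (effect size = 0.3) between the intervention and control groups", and specifies that this is "with respect to the Patient Safety Thermometer score". The number of wards then follows "with an average cluster size of 25 patients and assumed ICC of 0.05, 32 wards will be required (16 per arm"). The ICC is defended in these terms: "This estimate of ICC seems reasonable for a trial in secondary care with a patient reported outcome".

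Other sections describe the Thermometer score differently:

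- 'Primary outcome measures' presents it as routine data that every ward must return monthly on four kinds of harm, condensed into one harm-free percentage (0 to 100) per ward. The PMOS domain scores are listed beside it as a further primary outcome.
- 'Setting and sample' says "the outcome measures are at ward-level meaning that the unit of analysis is the ward". It describes the 25 patients per ward as those recruited to the study at each time point.
- 'Trial analysis' specifies a linear regression for harm-free care at 12 months, adjusted for the minimisation factors and baseline harm-free care, and adds: "As the outcome measure is on a ward level, no adjustment for clustering is required". The PMOS domains instead get linear mixed models with ward random effects.

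**The concern.** The inputs and the named outcome do not belong together. A cluster size of 25, an ICC and a patient-reported outcome describe the PMOS interviews. The Thermometer is not reported by patients, and nothing links its denominator to the 25 recruited patients. Its analysis contains no patient-level observations.

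The standardised effect of 0.3 is also ambiguous, because the SD that scales it is not named. 'Trial analysis' promises a standardised effect size for the ward-level comparison, and a reader will naturally set that figure against the planned 0.3. The two may be on quite different scales.

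This is the only power justification in the article, and it is given for a primary outcome. If harm-free care shows no difference, the trial could be reported as having had 80% power against a small to medium effect on it. The article does not support that statement.

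**Working it through.** **Inputs from the article.** Effect size 0.3, power 80%, alpha 0.05, 25 patients per ward, ICC 0.05, 16 wards per arm ('Estimate of sample size'); one value per ward, regression on wards, baseline as covariate ('Primary outcome measures', 'Trial analysis').

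**Not given, so assumed where used.** The SD behind the 0.3, the ward-level SD, the Thermometer denominator and ICC, the harm-free rate, and the correlation between baseline and 12 months.

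**1. Reproduce the stated figure.**
- Patients per arm without clustering: 2(1.960 + 0.8416)² / 0.3² = 174.4.
- Design effect: 1 + (25 − 1) × 0.05 = 2.2.
- Wards per arm: 174.4 × 2.2 / 25 = 15.3, rounded up to 16, so 32 in all.

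The figure reproduces with two-sided alpha. One-sided alpha gives 138 × 2.2 / 25 = 12.1, or 13 per arm, and does not. The calculation is a patient-level cluster calculation, with 0.3 in patient-level SDs.

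**2. Reading A: 0.3 is in SDs of the ward score that is analysed.** Two groups of 16 values, noncentrality 0.3 × √(16/2) = 0.85, 30 df: power 13.0% (13.3% by the normal approximation). About 175 wards per arm would be needed for 80%. Baseline adjustment raises the effective effect to 0.3/√(1 − ρ²), with 29 df:

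| Assumed ρ | Effective effect | Power |
|---|---|---|
| 0 | 0.300 | 13% |
| 0.5 | 0.346 | 16% |
| 0.7 | 0.420 | 21% |
| 0.8 | 0.500 | 28% |
| 0.9 | 0.688 | 47% |
| 0.95 | 0.961 | 75% |

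Reaching 80% needs ρ of about 0.956.

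**3. Reading B: 0.3 is in patient-level SDs.** Assume each ward percentage rests on 25 patients with ICC 0.05.
- SD of a ward value, in patient-level SDs: √(0.05 + 0.95/25) = √0.088 = 0.297.
- Effect on the analysed scale: 0.3 / 0.297 = 1.01 ward-level SDs.
- Power: 79% (t, 30 df) or 82% (normal).

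This depends on the assumed denominator and ICC. With 15 patients and ICC 0.10, the effect is 0.75 ward-level SDs and power 54%; with 30 patients and ICC 0.01, it is 1.45 and 98%.

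**4. Detectable difference with 16 wards per arm at 80% power.** 1.02 residual ward-level SDs (t, 30 df; 0.99 by the normal approximation). In unadjusted ward-level SDs this is about 1.02 × √(1 − 0.5²) = 0.88 at ρ = 0.5 and 1.02 × √(1 − 0.7²) = 0.73 at ρ = 0.7. The degrees of freedom spent on the minimisation factors are not deducted.

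**5. Illustration in percentage points, reading B only.** If harm-free status is treated as a binary patient-level variable, 0.3 × √(p(1 − p)) gives 12.0 points from an assumed 80%, 10.7 from 85% and 9.0 from 90% (to 99%). From 92% the 8.1 points would pass 100%. All these starting rates are assumptions.

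**The case against.** The best defence is that the section's own inputs settle the scale. Cluster size and ICC play no part if 0.3 is in ward-level SDs, and the 32 wards reproduce only on the patient-level scale. On that scale, analysing one summary per ward loses almost no power: 79% to 82%. The calculation also fits the PMOS domain scores, which are themselves primary. The planned 95% confidence interval for harm-free care would show how imprecise a null result is.

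Much of this stands, and it rules out several stronger conclusions that a reader might infer:

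- *That the trial has 13% power, or needs 175 wards per arm.* Both figures belong to reading A alone, and the 13% also ignores baseline adjustment.
- *That the planned effect means removing nearly all harm.* This would take the Background's "as many as one in 10 patients are harmed while receiving hospital care" as the Thermometer baseline. That figure concerns healthcare harm in general, whereas the Thermometer covers four items, and the article gives no harm-free rate.
- *That the trial can exclude only a very large effect.* One ward-level SD may be few percentage points if wards differ little, and the article gives no ward SD.
- *That the sample size arithmetic is wrong, or the trial underpowered overall.* The arithmetic is right, and nothing here weakens it for PMOS.

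The defence does not rescue the claim as written. Reading B needs a Thermometer denominator of about 25 and an ICC of 0.05 for harm-free status. The article states neither, and its only support for the ICC is that the outcome is patient reported, which the Thermometer is not.

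**Conclusion.** The point holds as a mismatch between a power claim and the outcome it names. The 80% figure is sound for a patient-level outcome with the stated inputs; for harm-free care it is unsupported on either reading. With 0.3 in ward-level SDs, power is about 13% without baseline gain and stays below 50% up to an assumed baseline correlation of 0.9. With 0.3 in patient-level SDs, roughly 80% may be right, but only on unstated assumptions, and the target is then about 1.0 SD of the variable analysed, which is not small to medium on that scale.

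What can be said from the design is that 32 ward values give 80% power for about 1.02 residual ward-level SDs. Its size in percentage points cannot be known from the article. A later analysis plan could supply the missing SD and correlation, but it could not make the stated ICC justification apply to the Thermometer.

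**What to change.** - State that the calculation with effect size 0.3, ICC 0.05 and 25 patients per ward applies to the PMOS domain scores, with 0.3 in patient-level SDs.
- For harm-free care, replace the 80% claim with the detectable difference for the regression on 32 wards: about 1.02 residual ward-level SDs at 80% power, or about 0.88 or 0.73 unadjusted SDs at assumed baseline correlations of 0.5 or 0.7.
- Convert this to percentage points using the ward-level SD from the baseline Thermometer data that the trial will collect. Label any earlier illustration, such as 9 points from 90%, as an assumption.
- Drop the small-to-medium and patient-reported descriptions where the Thermometer is meant.

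The cost is rewording the sample size section and carrying the same statement into the analysis plan. No wards or patients are added. The drawback is a less favourable stated sensitivity for harm-free care.
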